### 2.7. Statistical Analysis

Once data are obtained in the three research groups (HIIT, HIIT + PA, and CG) they will be compared at baseline, after 12 weeks of intervention, and three months after the end of the training program. Frequency tables will be obtained for the sociodemographic variables and means and standard deviations for the quantitative variables. The effects of the intervention on the primary and secondary outcomes will be evaluated with repeated measured analysis. The effect size (95% confidence interval), percentage of change, and statistical significance will be reported for each outcome with regards to the main group (between-subjects) time (within-subjects) and their interaction (group × time) effects.

Finally, various correlation analyses between the different variables will be carried out using Spearman’s Rho.

All data will be processed with the SPSS v.26 statistical program, establishing a confidence interval of 95% and estimating a significance level of *p* equal to or less than 0.05.

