## Abstract

Sedentary lifestyles have become a social problem, mainly among women. A sedentary lifestyle has been associated with poorer health in this population, negatively affecting physical and mental health. Physical exercise, in particular high-intensity interval training (HIIT), has been shown to be a neuroprotective tool. The present study provides a protocol design for a parallel-group Randomized Controlled Trial (RCT), whose aim will be to compare the effect of two physical interventions, HIIT and physical activity (increasing daily steps), on Insulin Growth Factor-1 (saliva IGF-1 concentrations), executive functions, quality of life, body composition, physical fitness, and physical activity in young sedentary women. At least 77 women will be recruited and randomly assigned to either a HIIT group (12-week exercise HIIT intervention, 3 sessions/week), the HIIT + PA group (12-week exercise HIIT intervention, 3 sessions/week, plus 10,000 steps/day), or a control group (usual care). The primary outcome measure will the chronic change in IGF-1 concentration levels measured in saliva. Secondary outcome measures will be: (i) executive functions; (ii) body composition; (iii) physical fitness; (iv) physical activity; and (v) quality of life. All outcomes will be assessed at the beginning of the study, after the intervention, and after three months of follow-up. After this intervention, we will be able to determine whether HIIT together with increased physical activity could be more effective than HIIT alone in IGF-1 stimulation. Furthermore, by comparing both intervention groups, we will be able to determine the differential effects on numerous health-related variables. Consequently, the conclusions of this study could help better understand the effects of a training program on IGF-1 concentration levels and executive functions. In addition, various strategies could be proposed through physical exercise to improve cognition in this age group, as well as to improve the health status of this sedentary population.

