### 2.3. Sample Size

The sample size will be calculated in an a priori analysis (G*Power V.3.1.9.6) on the basis of the change in IGF-1 levels with reference to the results of the Antonelli et al. study [22]. This study will require a sample size (for each group) of 37 (41, assuming a subject loss of 10%). This is for an alpha = 95%, a statistical power of 80% and a precision (d) of 5.23. According to the objectives and design of the study, and to form three groups of subjects, the subjects will be randomly distributed into two experimental groups (HIIT and HIIT + PA) and a control group (CG). All groups will be made up of healthy female university students who are all sedentary and inactive and willing to participate in the study.

To attain this number of female university students, recruitment will be carried out through online dissemination via the institutional website of the University of Seville, e-mails and social networks. Once all female students with interest in participation are registered, different information sessions will be scheduled prior to the start, during which the inclusion and exclusion criteria will be applied. In this way, a greater homogeneity of the sample will be obtained, and it will be possible to achieve a reduction of possible biases.

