### 2.6. Primary and Secondary Outcomes

#### 2.6.1. Primary Outcomes

##### Insulin Growth Factor-1 (IGF-1) 

The main biochemical determinants established in this study will be measured in saliva. Thus, the magnitude of the IGF-1 response in saliva as a consequence of the execution of a 12-week HIIT training program will be analyzed. Furthermore, the acute response to maximum effort will be measured in the initial and final evaluations.

Saliva will be collected in a fasting state (between 8–12 h) and the passive drooling method will be used. At each assessment, a saliva sample will be obtained at rest and after the maximum effort. For this collection, participants will be asked to tilt their head forward and accumulate saliva. When they have a sufficient amount of saliva, they will be asked to drool in a 10 × 10 test tube. After collection, the samples will be centrifuged at 1650× *g* at 4 °C for 10 min. They will then be aliquoted and stored at −80 °C within one hour of collection. To measure the variability in each IGF-1 concentration assessment in saliva, the ELISA KIT protocol will be used.

Circulating IGF-1 levels (ng/mL) will be determined in saliva by an enzyme-linked immunosorbent assay (ELISA) and performed in duplicate. Samples will be added to the wells of the microtiter plate with the IGF-1 specific antibody. Horseradish Peroxidase (HRP)-conjugated Avidin will then be added to each well of the microplate and incubated. After adding the TMB substrate solution, only the wells containing IGF-1 will show a color change. This action will be measured spectrophotometrically at a wavelength of 450 nm ± 10 nm. The concentration of IGF-1 in the samples will be determined by comparing the concentration of the samples with the standard curve.

In this case, kits produced by Elabscience will be used, with the following characteristics (Table 2):

Before starting the measurement, the standards that will later be used in the design of the standard curve necessary for the calculation of the results must be reconstituted. For this purpose, 7 tubes with 0.5 mL of diluent buffer will be prepared and the diluted standard used to produce a double dilution series.

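### The three-visit repeated-measures analysis reads most naturally as a repeated-measures ANOVA; run that way in SPSS, it would drop a woman's 12-week IGF-1 value if she missed only the three-month visit

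*Protocol article*

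**What the plan says.** All of the following comes from the protocol article.

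- **Analysis (Section 2.7).** "The effects of the intervention on the primary and secondary outcomes will be evaluated with repeated measured analysis". Results are to be reported for the "main group (between-subjects) time (within-subjects) and their interaction (group × time) effects".
- **Visits (Section 2.7).** The three groups' data are such that "they will be compared at baseline, after 12 weeks of intervention, and three months after the end of the training program". The Abstract agrees: "All outcomes will be assessed at the beginning of the study, after the intervention, and after three months of follow-up".
- **Software (Section 2.7).** "All data will be processed with the SPSS v.26 statistical program, establishing a confidence interval of 95" per cent. No procedure within SPSS is named.
- **Primary outcome.** The Abstract says "The primary outcome measure will the chronic change in IGF-1 concentration levels measured in saliva". Section 2.6.1 refers to the salivary IGF-1 response "as a consequence of the execution of a 12-week HIIT training program will be analyzed". No single primary time point is fixed, but this wording supports reading week 12 as the main one.
- **Sample size (Section 2.3).** "This study will require a sample size (for each group) of 37 (41, assuming a subject loss of 10" per cent). The visit by which that loss is counted is not stated.
- **Accelerometry (Section 2.6.2).** A recording counts only with at least 4 full days of 8 hours' wear, one of them at the weekend.

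**The concern.** A between-subjects factor, a within-subjects factor and their interaction are the terms of a repeated-measures ANOVA. Nothing in Section 2.7 points elsewhere: it mentions no random effects, no covariance structure and no use of partial records. In SPSS, the repeated-measures ANOVA reads one row per woman with a column for each visit, and it discards the whole row if any column is empty. Estimates and contrasts taken from that model rest on the same reduced set.

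Two things follow if the analysis is run that way.

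- A woman who completes the programme and gives valid baseline and 12-week samples, but does not return three months later, is removed from the 12-week comparison. Whether her primary value counts then depends on a visit that takes place after the effect of main interest has been measured.
- A woman with too few valid accelerometer days at one visit is removed from the accelerometry analysis at every visit.

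At stake are precision at 12 weeks and, if returning for follow-up is related to outcome, the validity of the 12-week estimate. Under complete-case analysis the single 10% allowance would also have to cover everyone who misses any visit.

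**Working it through.** **Inputs from the document.** 37 per group before loss, 41 after; 10% loss; 80% power; a difference of 5.23 (all Section 2.3); three visits (Section 2.7).

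**Assumptions.** Two-sided 5% level; one pairwise contrast at week 12; equal groups. No standard deviation is given, so the standardised effect is back-solved from 37 per group at 80% power. The 80% at 37 is therefore true by construction and does not check the plan.

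**1. The plan's own figure.** 37 × 1.1 = 40.7, rounded up to 41. Dividing instead, 37 / 0.9 = 41.1, rounded up to 42. The stated 41 is reproduced by the first route and is within one woman of the second. In reverse, 41 × 0.9 = 36.9.

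**2. Implied effect.** Normal approximation: d = (1.960 + 0.842) / √(37/2) = 0.651, which with 5.23 implies an SD of 5.23 / 0.651 = 8.03. The exact two-sample t calculation gives d = 0.660.

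**3. Power at week 12 when only complete cases count.** Power ≈ Φ(0.651 × √(n/2) − 1.960), with loss at random.

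| Missing only the follow-up | If 10% are already lost by week 12 (36.9 seen): complete cases per group | Power | If all 41 are seen at week 12: complete cases per group | Power |
|---|---|---|---|---|
| 0% | 36.9 | 79.9% | 41.0 | 83.9% |
| 5% | 35.1 | 77.8% | 38.9 | 82.0% |
| 10% | 33.2 | 75.6% | 36.9 | 79.9% |
| 20% | 29.5 | 70.6% | 32.8 | 75.1% |
| 30% | 25.8 | 64.8% | 28.7 | 69.4% |

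The exact t calculation with d = 0.660 gives 80.0% at 37 and 75.2% at 33. In the 10% row, 3 × (36.9 − 33.2) ≈ 11 women with valid 12-week data are discarded, or 3 × (41 − 36.9) ≈ 12 in the right-hand case. A model that keeps partial records discards none of these values.

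The Abstract's total of 77 (25.7 per group) does not fit three groups of 37 or 41 (111 or 123). That is a separate matter. At 25.7 per group the same calculation gives 64.6%, falling to 60.0% with 10% missing only the follow-up, so the cost is again about 5 points.

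**4. Bias.** Under random loss there is none: a simulation with 41 per group and 20% missing the follow-up gave a 12-week difference of 5.26 with all data and 5.26 with complete cases.

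For loss related to outcome, let the week-12 change X be N(0.66, 1) in a training arm and N(0, 1) in control. Let the chance p(X) of missing the follow-up be logistic in X, with smaller gains more likely to be lost. The mean among women kept is E[X(1 − p)] / E[1 − p].

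| Mechanism | Slope −0.5 per SD | Slope −1 per SD |
|---|---|---|
| Outcome-related in the training arm only (about 12% and 11% lost), 15% lost at random in control | 0.72 | 0.76 |
| Same outcome-related mechanism in both arms, set so that control loses 15% | 0.64 | 0.61 |
| True difference | 0.66 | 0.66 |

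The error is upward in the first case and downward in the second. The document does not say which, if either, applies.

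**The case against.** The strongest reply is that Section 2.7 never names ANOVA or the general linear model procedure. A linear mixed model is also a repeated-measures analysis; it reports the same three effects and is available in SPSS v.26. On that reading nobody is deleted. A condensed article may also leave the procedure and the handling of missing visits to a fuller protocol or analysis plan that is not shown here.

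Much of this stands. Deletion cannot be stated as fact, and the absence of a missing-data rule is not criticised. What remains is that the layout the article does state points to the method that deletes. If a mixed model is meant, the wording misleads; if ANOVA is meant, valid data are lost. The same clarification settles both.

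Four stronger readings are tempting, and the document does not support them.

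- *That the groups are not compared as randomised.* No text removes anyone from her assigned group.
- *That loss will be unequal because contact is unequal.* The supervised sessions and the calls after non-attendance belong to the 12-week programme. The loss at issue comes afterwards, when no supervised sessions are described in any arm.
- *That deletion inflates the effect.* This needs outcome-related loss in the training arm only; the same mechanism in both arms gives mild attenuation.
- *That the planned power is necessarily missed.* If the 10% means total loss by the last visit, 41 × 0.9 ≈ 37 complete cases remain and power is about 80% even under ANOVA. Valid 12-week data would still be wasted.

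**Conclusion.** The point holds conditionally. As worded, Section 2.7 most naturally describes a repeated-measures ANOVA. If it is run that way, women who miss only the three-month visit lose their 12-week IGF-1 values, and one poor accelerometer week removes a woman from all accelerometry comparisons.

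The illustrated cost is about 5 percentage points of 12-week power (about 80% to about 75%). It rests on a back-solved effect size, on an assumed further 10% missing only the follow-up, and on reading week 12 as the main time point, which the article supports but does not state. Any bias depends on a dropout mechanism that the document does not give, so neither its presence nor its direction can be asserted. The change is worth making because a better method is available in the same software at almost no cost.

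**What to change.** **Section 2.7.** Specify a linear mixed model for repeated measures (MIXED in SPSS v.26). Use group, visit and group × visit as fixed effects and an unstructured within-woman covariance. Include every available visit of every randomised woman in her assigned group. With three visits the unstructured covariance has only six parameters (three variances and three covariances).

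**Section 2.3.** State the visit to which the 10% loss applies.

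**Cost.** About one paragraph of wording and slightly more analysis work; no added participants, visits or software. The mixed model relies on missing values being missing at random given the observed data. That is an assumption, but a weaker one than complete-case analysis needs.

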Physical exercise has proven to be a useful strategy to improve performance in executive functions in adults [12]. This positive impact may be due to its effect on plasticity and neuronal growth. In fact, physical exercise leads to increased cerebral blood flow, increased neurogenesis stimulation, optimized synaptic interconnections, and increased generation of neurotrophic factors such as IGF-1 [13]. IGF-1 has been shown to be a potent facilitator of brain plasticity in young adults. Thus, a higher concentration of IGF-1 may be conducive to higher brain performance and better cognition [14].

Despite these effects of physical exercise on executive functions and IGF-1 concentrations, it is known that, depending on the type of physical exercise performed, its effect may lead to different results. However, the intensity variable appears to be an important element in generating greater stimulation of IGF-1 [15]. Low–moderate intensity exercise has shown some chronic benefits in both IGF-1 concentration and executive functioning. In contrast, high-intensity exercise has shown greater performance for both variables. 

In recent years, due to the significant increase in the practice of HIIT in society [16], there has been a high level of interest in knowing its effect on different health variables, such as physical and psychological fitness [17], cardiometabolic parameters such as glycemic control, and even cognitive functions [15]. These studies show that HIIT is an efficient strategy to improve all these health-related variables. However, there is little evidence comparing the combination of a HIIT training program with an increase in light physical activity (daily steps) versus performing only the HIIT training program, or analyzing its effect on physical fitness, mental health, and quality of life in the population described.

Therefore, the hypothesis of the study is that a 12-week HIIT program implemented with an increase in daily physical activity (HIIT + PA) enhances to a greater extent executive functions, IGF-1 concentration, physical condition, body composition, and quality of life in sedentary young women than a similar program (HIIT) alone.

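### The group, time and group × time effects fixed for reporting do not test the stated hypothesis that HIIT + PA is better than HIIT alone; the direct contrast should be named as primary

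*Protocol article*

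**What the plan says.** The hypothesis in the Introduction (section 1) is a directional comparison of two arms. It holds that the combined intervention "enhances to a greater extent executive functions, IGF-1 concentration, physical condition, body composition, and quality of life in sedentary young women than a similar program" consisting of HIIT alone. The Abstract says the trial will determine "whether HIIT together with increased physical activity could be more effective than HIIT alone in IGF-1 stimulation", and defines the main endpoint thus: "The primary outcome measure will the chronic change in IGF-1 concentration levels measured in saliva".

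Section 2.7 sets out the analysis. The three groups are to be "compared at baseline, after 12 weeks of intervention, and three months after the end of the training program". The method is given in one sentence: "The effects of the intervention on the primary and secondary outcomes will be evaluated with repeated measured analysis". Effect size with confidence interval, percentage change and significance are then to be reported for each outcome "with regards to the main group (between-subjects) time (within-subjects) and their interaction (group × time) effects".

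Section 2.7 names no HIIT + PA versus HIIT contrast, no primary time point and no adjustment for baseline. Section 2.6.1 ties the IGF-1 response to the 12-week programme and collects saliva both at rest and after maximal effort.

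**The concern.** With three arms and three visits, the reported effects have 2 (group), 2 (time) and 4 (group × time) degrees of freedom. The hypothesis concerns one difference, with 1 degree of freedom, and none of the three tests isolates it.

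- **Group × time** asks whether the three mean profiles are parallel. It can be significant because control differs from both HIIT arms, even if those two arms are identical.
- **Group** has the same weakness. It also averages in the baseline visit, which section 2.4 places before randomisation, when no treatment difference can exist.
- **Time** pools the arms and compares none of them.

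The risk is one of interpretation. The trial could report significant effects for IGF-1 with no pre-named test showing whether the added steps contributed anything. If the pairwise test is chosen after the data are seen, there are three pairs of arms and two post-baseline visits to choose from.

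**Working it through.** **Inputs from the article.** Three arms and three visits (2.7); 37 per group at 80% power, with a stated precision of 5.23 (2.3). Alpha is printed as 95% and is read here as two-sided 0.05.

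**Inputs assumed.** The article gives no SD and no correlation between visits. Effects are therefore in SD units, with equal correlation of 0.5 or 0.7 between visits and equal arm sizes.

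**Scale of effect.** The 37 cannot be reproduced without an SD, only solved backwards: SMD = (1.960 + 0.842) × √(2/37) = 0.651. If 5.23 is a raw difference, the SD is 5.23/0.651 = 8.03. The 0.66 SD used below is close to this.

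**Case A: the hypothesis is false.** Means at baseline, 12 weeks and follow-up are 0, 0, 0 for control and 0, 0.66, 0.33 for each HIIT arm.

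- HIIT + PA minus HIIT is 0 at every visit.
- Marginal means: visits 0, 0.44, 0.22; arms 0, 0.33, 0.33; overall 0.22.
- Interaction terms: control 0.22, −0.22, 0; each HIIT arm −0.11, 0.11, 0.
- Sum of squares: 2 × 0.22² + 4 × 0.11² = 0.0968 + 0.0484 = 0.1452.
- Noncentrality = 37 × 0.1452/(1 − ρ) = 10.7 at ρ = 0.5 and 17.9 at ρ = 0.7, on 4 and 3 × 36 × 2 = 216 df. All of it comes from control.

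Simulated rejection rates (4,000 trials per setting):

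| Test | ρ = 0.5 | ρ = 0.7 |
|---|---|---|
| Group × time | 75% | 93% |
| Time | 99% | 100% |
| Baseline-adjusted HIIT + PA vs HIIT at 12 weeks | about 5% | about 5% |

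**Sensitivity to the assumed profile.** With 0.651 SD fully retained at follow-up (2,000 trials per setting), rates at ρ = 0.5 and 0.7 are:

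| Truth, 37 per arm | Group × time | Adjusted contrast |
|---|---|---|
| Steps add nothing | 85%, 98% | 5%, 5% |
| Steps add half the HIIT effect | 99%, 100% | 35%, 49% |
| Steps add the full HIIT effect | 100%, 100% | 89%, 97% |

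The interaction is usually significant in every row, so it says little about which row is true.

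**Dilution of the group effect.** In case A, each HIIT arm differs from control by (0 + 0.66 + 0.33)/3 = 0.33 SD averaged over visits, half the 12-week difference.

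**Value of baseline adjustment.** For a true HIIT + PA minus HIIT difference of 0.66 SD at 12 weeks, the variance per woman is 2(1 − ρ) for change scores and 1 − ρ² with baseline as covariate. The ratio is (1 + ρ)/2. Approximate power is Φ(0.66/√(2v/37) − 1.96):

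| ρ | Analysis | v | SE | Power by formula | Power by simulation |
|---|---|---|---|---|---|
| 0.5 | Change score | 1.00 | 0.232 | 81% | 78–80% |
| 0.5 | Baseline-adjusted | 0.75 | 0.201 | 91% | about 90% |
| 0.7 | Change score | 0.60 | 0.180 | 96% | about 95% |
| 0.7 | Baseline-adjusted | 0.51 | 0.166 | 98% | about 97% |

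**The case against.** The strongest reply is that the comparison is announced and only its detail is absent. Section 2.7 says the three groups will be compared at each visit, and the Abstract speaks of comparing the two intervention groups. Pairwise tests after a group × time test are routine, and an analysis plan that is not shown may contain them. This stands in part: the comparison is foreseen in general terms. But section 2.7 does say which effects will carry significance, and the one the hypothesis needs is not among them.

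Second, the pairwise hypothesis is not the only aim. Section 2.6.1 and the Discussion also describe determining the effect of a HIIT programme on IGF-1, and with an inactive control group × time partly serves that aim. This stands. A reader might infer that the analysis answers none of the trial's questions; the article does not support that.

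Third, the 75% to 93% might be read as a false-positive rate. It is not, because in that scenario both HIIT arms truly differ from control and the test is right to reject. It would mislead only if taken as evidence for the added steps, and the article nowhere says it will be.

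Two further inferences are tempting and should be resisted. Nothing in section 2.7 says that women missing a visit will be dropped, since a repeated-measures analysis may equally be a mixed model. Practice effects on the cognitive tests, and regression to the mean after selection on low reported activity, are not shown to bear on salivary IGF-1.

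Finally, keeping baseline as one of the repeated outcomes is valid under randomisation. Using it as a covariate is a matter of precision, and the gain is small when the correlation is high.

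**Conclusion.** The concern holds as a mismatch between the stated hypothesis and the effects fixed for reporting; it should be fixed. The logical point needs no assumed values: an omnibus test over three arms cannot show which arms differ, and a time effect compares none.

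The size is illustrative. The interaction figures rest on an assumed standardised effect, correlation and retention at follow-up: about 75% to 93% with half retained and 85% to 98% with full retention, when HIIT + PA adds nothing over HIIT. The benefit of baseline adjustment likewise depends on the correlation, from about 10 percentage points of power at 0.5 to about 2 at 0.7.

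Twelve weeks is not labelled as the primary time point. It follows from section 2.6.1, and taking the resting sample as the measure of chronic change is the natural reading of the endpoint.

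**What to change.** In section 2.7:

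1. Name the primary test: HIIT + PA minus HIIT in resting salivary IGF-1 at 12 weeks, adjusted for baseline IGF-1, with its 95% confidence interval. A contrast from a mixed model for the post-baseline visits, with arm, visit, arm × visit and baseline IGF-1, would serve.
2. List HIIT versus control and HIIT + PA versus control as the next contrasts. These cover the aim of showing an effect of HIIT itself.
3. State that the group, time and group × time effects will not be taken as evidence for the hypothesis.

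The essential step is the first, naming the contrast. The baseline covariate is a free gain in precision. The cost is a few sentences: the data are already to be collected, and the SPSS version named in the article can fit the model.
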